## Abstract

**Background:**

Modified sport interventions run by physiotherapists have shown potential as cost-effective, engaging, and effective interventions to improve gross motor skills and support transition to real-world sports participation for children with cerebral palsy. At present, this population demonstrates decreased participation in physical activities and sport compared to peers due to barriers ranging from body function to accessibility challenges. Sport provides culturally relevant opportunities for social integration, community participation and physical activity and has been shown to improve the fitness, self-esteem, confidence and quality of life of children with disabilities. The *Sports Stars* physiotherapy group has been designed to support the development of a range of fundamental movement and sports skills through activity skill practice and participation in modified popular Australian sports.

**Methods:**

This randomised, waitlist controlled, assessor blinded, superiority trial with two parallel groups will aim to compare the effectiveness of *Sports Stars* to standard care across all ICF domains. Children in the *Sports Stars* group are expected to demonstrate greater improvement in their individually-selected, sports related goals measured by the Canadian Occupational Performance Measure. This study will aim to assess sixty ambulant children aged six to 12 years with a diagnosis of cerebral palsy. Children will be excluded if they have had recent Botox or neurological/orthopaedic surgery. The *Sports Stars* intervention includes eight, one-hour, weekly physiotherapy group sessions with four to six participants and one lead physiotherapist. Outcome measures will be collected pre, post and 12 weeks post the immediate *Sports Stars* group to assess change immediately after, and at follow up time points*.*

**Discussion:**

This will be the first study of its kind to investigate a culturally relevant sports-focussed fundamental movement skills physiotherapy group for ambulant children with cerebral palsy. The findings will add to a growing pool of evidence supporting group physiotherapy for children with cerebral palsy and the *Sports Stars* group will provide an avenue for children to transition from individual physiotherapy to mainstream and modified recreational and competitive sports.

**Trial registration:**

Australian New Zealand Clinical Trials Registry: ACTRN12617000313336 Registered 28, February 2017.

WHO Universal Trial Number: U1111–1189-3355 Registered 1, November 2016.

**Electronic supplementary material:**

The online version of this article (10.1186/s12887-018-1190-z) contains supplementary material, which is available to authorized users.

## Background

Cerebral palsy (CP) is defined as a “*group of permanent disorders of the development of movement and posture, causing activity limitations that are attributed to non-progressive disturbances that occurred in the developing fetal or infant brain*” [1]. Children with CP demonstrate limitations across all International Classification of Functioning, Disability and Health (ICF) domains. They frequently exhibit body function challenges including spasticity, weakness, tightness and poor motor control leading to limitations in balance, coordination and fitness [2]. Around 59.5% of Australian children with CP are classified as level I-II on the Gross Motor Function Classification System- Expanded and Revised (GMFCS- E&R) [3]. Although these children walk without aids, they experience limitations in gross motor function, particularly in complex locomotor or object control activity skills. Children with ambulatory CP frequently fail to meet minimum physical activity guidelines [4, 5], and are even less active than their typically developing peers, with decreased frequency of participation in a more limited number of mainstream physical leisure, self-care and productivity activities, including sport [6–11].

Sport is recognised as an important part of Australian culture and is a common avenue for children to increase their physical activity [12]. For the purpose of this study, sport is defined as “*A human activity involving physical exertion and skill as the primary focus of the activity, with elements of competition where rules and patterns of behaviour governing the activity exist formally through organisations and is generally recognised as a sport* [13]*.”* Sports participation provides opportunities for social integration, community participation and physical activity and has been shown to improve the fitness, self-esteem, confidence and quality of life of children with disabilities [14, 15]. The cultural importance of sport for Australian children means that it is of even greater importance for children with disabilities to have equitable opportunities to develop gross motor function through participation in sport. Carlon [4] suggests that maintaining changes to health-related fitness requires improved physical activity behaviours in the home, school and community. Sport is one avenue to achieve this, and sports participation has been considered an alternative to prolonged physiotherapy intervention in adolescence and into adulthood [16]. By their nature, sport and physical activity interventions are more likely to occur in group formats, and children with CP who participate in group interventions have demonstrated increased engagement, motivation and participation compared to individual interventions [17–20] along with high levels of translation to real-world sports participation [21, 22]. Additionally, compared to individual physiotherapy, group physiotherapy can be more cost effective in providing the same therapy dose [23, 24].

Although participation of children with CP in sports has increased [25], numerous barriers to participation persist, including children’s physical ability and fatigue, accessibility of appropriate sporting opportunities and facilities, and acceptance of the child’s disability [26, 27]. Decreased experience and proficiency in fundamental movement skills is a particularly strong barrier to children’s ability to perform, and subsequently participate in, physical activity [28] as well as adversely affecting lifelong physical activity patterns [4, 29]. The SPORTS Participation Framework developed by the authors (Fig. 1) proposes a pathway for children to participate in recreational, competitive and elite level sport. Despite the evidence confirming barriers to participating in sport, there are limited opportunities for children with CP to transition from individual physiotherapy, to participating in recreational or competitive sport. A recent systematic review by our group investigating active exercise interventions targeting gross motor function in school-aged, ambulant and semi ambulant children with CP, identified Modified Sports as a promising intervention requiring further high-level research [30].

**Fig. 1 Fig1:**
[figure not shown]
SPORTS Participation Framework for children with disabilities

There is currently limited availability of, or evidence for, culturally relevant modified sport interventions for children with CP, with two of three low-level Modified Sport interventions identified investigating winter sports irrelevant to the Australian climate [22, 31]. *Sports Stars* targets the development of a range of fundamental movement and sports skills through activity skill practice and participation in modified popular Australian sports; soccer, netball, T-ball and cricket. This randomised controlled trial of the *Sports Stars* program will aim to fill this gap in the literature by investigating the effect of a culturally relevant, sports-oriented, group physiotherapy intervention on sports related body function, activity and participation.

## Methods/Design

### Study aims

The proposed study is a randomised, waitlist controlled, assessor blinded, superiority trial with two parallel groups. This study will aim to compare the effectiveness of a group-based, sports oriented physiotherapy intervention, *Sports Stars,* for ambulant school-aged children with CP, to standard care across all ICF domains. This study will also aim to gain feedback from treating physiotherapists and caregivers involved in the study to determine the acceptability of the intervention. The specific hypotheses to be tested are:

### Primary hypothesis

**H1:** Compared to children in the standard care group, children in the *Sports Stars* group will demonstrate greater improvement in their individually-selected, sports activity and participation related goals measured by the Canadian Occupational Performance Measure (COPM).

### Secondary hypotheses

**H2: Body function and structure:** Compared to children in the standard care group, children in the *Sports Stars* group will demonstrate greater improvements in lower limb and upper limb strength, balance, agility and their aerobic and anaerobic fitness.

**H3: Activity:** Compared to children in the standard care group, children in the *Sports Stars* group will demonstrate greater improvements in gross motor capacity, including locomotor ability and object control skills.

**H4: Participation:** Compared to children in the standard care group, children in the *Sports Stars* group will demonstrate increased participation in physical activities including recreational or formal sporting activities.

**H5: Quality of life:** Compared to children in the standard care group, children in the *Sports Stars* group will demonstrate greater improvements in quality of life as measured by parent report.

### Study sample and recruitment

#### Inclusion criteria

This study will include children who:Are aged 6–12 years at study entry;Have a confirmed diagnosis of CP;Are ambulant without aids (classified as GMFCS- E&R Level I or II);Can commit to eight, one-hour weekly group physiotherapy sessions and three, two-hour assessment appointments over a period of 6 months.

#### Exclusion criteria

Children will be excluded from the study if they:Are unable to complete baseline assessments;Have had orthopaedic or neurological surgery within 6 months prior to the immediate intervention start date;Have had Botulinum Toxin injections within 3 months prior to the immediate intervention start date;Have intellectual or behavioural difficulties which would limit their ability to participate in the assessment or therapy protocols;Have medical co-morbidities which prevent them from exercising safely (e.g. cardiac or respiratory instability, uncontrolled seizures).

### Criteria for withdrawal

Participants will be excluded from the study if they fail to attend either their baseline assessment or withdraw prior to the commencement of the immediate *Sports Stars* group. Primary analysis will use the intention to treat principle, using the last observation carried forward for participants who withdraw after commencement of intervention in the immediate *Sports Stars* group.

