#### Recruitment process

Eligible children will be prospectively recruited through the client database of a state-wide community rehabilitation service. As geographical location and participant availability are critical to forming groups of sufficient participant numbers for this study, participants will be recruited in blocks according to their geographical location. Once at least four, and a maximum of six, children are identified that can attend an eight-week group on a specified day in a specific geographical location, these children will be assigned as group one. When a second group of four to six children are identified for a geographical location, they will be assigned as group two. When two groups of four to six participants each are identified, they will proceed to randomisation.

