#### Randomisation

A random sequence will be generated via coin flip by an independent, off-site co-investigator (MA) who will not be involved with assessment or treatment (as per process used in previous studies [17]). The outcome (heads: group 1 = immediate *Sports Stars* intervention, group 2 = waitlist *Sports Stars* intervention. Tails: group 1 = waitlist *Sports Stars* intervention, group 2 = immediate *Sports Stars* intervention) will be written on a piece of paper and concealed inside a sequentially numbered, opaque envelope and stored securely off-site.

When two groups are identified, they will be randomly assigned to either the immediate intervention group or the waitlist control group with a 1:1 block allocation via drawing of one of the opaque envelopes. Randomisation will be completed offsite by the same independent co-investigator (MA). This process will continue until 60 participants complete baseline assessments and proceed to the *Sports Stars* group.

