## Analyses

Statistical analysis will be performed using SPSS statistical software. Primary analysis will use the intention to treat principle, using the last observation recorded for participants who withdraw from the program.

Baseline data will be reported using descriptive statistics for each variable (individual sports related activity and participation goals, GM capacity, aerobic fitness, anaerobic fitness and agility, functional strength, participation and quality of life) to establish any difference between randomised groups. The method of aggregation will depend on the normality of the data and will include the mean and standard deviation (normally distributed data) or the median and interquartile range (non-normally distributed data). If characteristics are not comparable at baseline, they will be modelled as covariates in subsequent analyses in order to adjust their possible confounding effects. Linear mixed models will be used to evaluate the effectiveness of the *Sports Stars* intervention compared to the waitlist control on the primary outcome (COPM). Linear mixed models take into account variation in individuals over time, are able to manage missing data without excluding participants for further analysis and examine changes in the outcomes over time as well as across the two groups. Significance will be set at *p* < 0.05. Residuals of the fitted models will be examined to ensure that all required assumptions are met.

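### Children who withdraw between randomisation and the start of the immediate group are excluded from the study, so the primary analysis is modified intention to treat, not intention to treat as labelled

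*Protocol article*

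**What the plan says.** Four sections of the protocol article bear on this.

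- **Recruitment process** sets the moment of randomisation: "When two groups of four to six participants each are identified, they will proceed to randomisation". The text asks only that the groups be formed; it does not mention a completed baseline.
- **Randomisation** describes the draw: "When two groups are identified, they will be randomly assigned to either the immediate intervention group or the waitlist control group". It then gives the stopping rule: "This process will continue until 60 participants complete baseline assessments and proceed to the" Sports Stars group.
- **Criteria for withdrawal** gives the exclusion: "Participants will be excluded from the study if they fail to attend either their baseline assessment or withdraw prior to the commencement of the immediate" group. The next sentence claims intention to treat, "using the last observation carried forward for participants who withdraw after commencement of intervention in the immediate" group. Carrying forward is thus provided only for children lost after the immediate group has begun.
- **Analyses** repeats the label without that limit: "Primary analysis will use the intention to treat principle, using the last observation recorded for participants who withdraw from the program".

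Under Study aims the design is a "randomised, waitlist controlled, assessor blinded, superiority trial with two parallel groups". No blinding of families is described. Under Sample size, 60 is the number to be recruited, which is a different counting point from the one under Randomisation.

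**The concern.** Intention to treat means that children are analysed as randomised. A rule that removes some of them after the draw defines a different population, and the label then tells readers that a protection is in place when it is not.

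Randomisation makes the two arms comparable at the draw. If families told to wait leave more often than families told to start, or if different kinds of families leave, the arms that remain are no longer the arms that were randomised. Because such a child is out of the study, T2 and T3 may never be collected, and a later analysis plan could not restore what was not measured. Counting the target of 60 after these losses also keeps them out of the headline number.

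**Working it through.** **Step 1. Order of events.** Two groups are formed (Recruitment process). An envelope is drawn and one group becomes immediate, the other waitlist (Randomisation). The immediate group later holds its first session. Before the draw there is no immediate group, so the period before it starts includes the interval from draw to first session. A child who leaves in that interval has been randomised and is excluded, in either arm.

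**Step 2. What is analysed.** The set consists of children who attended baseline and were still enrolled when the immediate group began. That is a modified intention-to-treat set.

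**Step 3. What happens to the count.** The stopping rule counts children who have gone on to the group. Losses before that point do not count towards 60, so further pairs of groups are recruited.

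**Step 4. The plan's own figure.** No stated figure bears on the exclusion rule, but the sample size supplies the scale.

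- Inputs (Sample size): SDs 1.87 and 2.88, difference 2 COPM points, alpha 0.05 (two-sided assumed, as sidedness is not stated), power 80%.
- Common SD = √((1.87² + 2.88²)/2) = 2.428.
- Normal approximation: n = 2 × (1.96 + 0.842)² × 2.428² / 2² = 23.1, so 24 per group.
- With the t distribution, power is 79.8% at 24 and 81.4% at 25. The stated 25 per group reproduces, and 50 × 1.2 = 60.

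**Step 5. Children left out.** With an assumed pre-start withdrawal fraction q, the number randomised for 60 to start is 60/(1 − q), rounded up.

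| q (assumed) | Randomised | Left out |
|---|---|---|
| 5% | 64 | 4 |
| 10% | 67 | 7 |
| 15% | 71 | 11 |
| 20% | 75 | 15 |

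**Step 6. Possible shift.** Suppose a fraction q of an arm is removed and those children would have changed d points less than the rest, whose mean is m. The mean over all randomised children in that arm is (1 − q)m + q(m − d) = m − qd, so removal moves the arm mean by qd. The contrast moves by the difference of the two arms' qd values, which is zero if they are equal. If only one arm loses children:

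| q (assumed) | d = 1 | d = 2 |
|---|---|---|
| 5% | 0.05 | 0.10 |
| 10% | 0.10 | 0.20 |
| 20% | 0.20 | 0.40 |

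The largest entry is 0.4/2 = 20% of the target difference. With 30 per arm, the standard error of the contrast is 2.428 × √(2/30) = 0.63, ignoring any correlation within groups.

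**The case against.** **The rule treats both arms alike.** It uses one calendar anchor, the start of the immediate group. Waitlist children who later decline their own programme are not excluded by it. The window may be short, and neither its length nor a withdrawal rate is given. This stands: bias is possible, not certain, and its direction is not fixed.

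**The size is assumed.** The fractions, the loss from one arm only, and the deficit in the excluded children are not in the article, and even the largest shift is below one standard error. This also stands. The figures show scale only. A systematic shift does not, however, shrink with sample size as the standard error does.

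**Some children cannot be analysed.** A child who never attends baseline has no COPM goals and nothing to carry forward. This is true of that part of the rule. It does not cover a child who attended baseline and then withdrew before the start.

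**A reader might infer that COPM goals are set in knowledge of the arm.** The recruitment text asks only that groups be formed before the draw, and the rule provides for a missed baseline, both of which suggest that baseline comes second. But the Exclusion criteria list inability to complete baseline assessment, which fits baseline as a screening step, and the flow chart (Fig. 2) is not available. Both arms are also offered the programme in the end, and all children must set sports-related goals, so a difference between arms in goal choice would be conjecture. The documents do not support stating that the primary outcome is contaminated.

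**A reader might infer child-for-child replacement.** The article does not say this. Losses are made up by recruiting new pairs of groups.

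**When families learn their arm is not stated.** That they must learn it before the immediate group starts follows from the design, since one group attends and the other waits.

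**Conclusion.** The contradiction stands on the text and does not depend on the missing flow chart. A stated exclusion removes randomised children while two sections call the analysis intention to treat, and the stopping rule makes up the losses through further recruitment. This is an explicit rule, not detail that an article leaves to a fuller document.

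The consequence is conditional. Bias needs pre-start withdrawal that differs by arm in number or type. That is plausible, since only the assessor is described as blinded and being told to wait is a reason to leave that exists in one arm only. Under assumed losses of 5–20% from one arm and a difference of 1–2 points, the shift is 0.05–0.4 COPM points in either direction against the 2-point target. If withdrawal is rare or alike in both arms, the estimate is little affected and the fault is chiefly one of labelling and counting.

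Whether baseline follows randomisation remains open. If baseline comes first, the missed-baseline clause is harmless and the withdrawal clause is still a post-randomisation exclusion.

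**What to change.** 1. Define the primary analysis set as every randomised child, in the allocated arm, whether or not the group was started.
2. Count the target of 60 at randomisation, and make the Sample size and Randomisation sections agree on this.
3. Replace exclusion from the study with withdrawal from the programme. Seek T2 and T3 from children who do not start, and report pre-start withdrawals by arm with reasons.
4. State the order of baseline and randomisation. If baseline now follows the draw, complete T1, including the COPM goals, before the envelope for that pair is opened. A missed baseline then becomes a pre-randomisation exclusion, no randomised child lacks goals, and goals are set without knowledge of the arm.
5. If the present set is of interest, keep it as a secondary analysis named modified intention to treat.

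**Cost.** The change is wording and, if needed, the order of two existing steps. T1 would be booked before allocation is known. Non-starters dilute the effect: if a fraction q of the immediate arm gained nothing, a 2-point effect would become 2 × (1 − q), that is 1.9 at 5% and 1.8 at 10%. Pre-start losses would also draw on the 20% attrition allowance unless T2 is obtained from those children.

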### Recruitment

#### Sample size

According to CONSORT guidelines, sample size calculations are based on adequate power for comparison between the effects of the *Sports Stars* program compared to standard care using the COPM immediately post intervention (T2). Data from a previous study investigating the effects of an exercise group aiming to improve physical activity, balance and strength in ambulant children with CP (6–14 years) showed a standard deviation of 1.87/2.88 (intervention/control) [32]. This standard deviation and a mean change of 2 points for performance on the COPM (clinically meaningful difference) were used to calculate sample size. Based on significance (alpha) of 0.05 and 80% power, a minimum sample of 25 participants in each group (50 participants total) will be required. Therefore, 60 participants (30 in each group) will be recruited to allow for 20% attrition.

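### Children who withdraw after allocation but before the immediate group starts are excluded from the study, although the primary analysis is called intention to treat

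*Protocol article*

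**What the plan says.** Four parts of the protocol bear on who is analysed.

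- **Criteria for withdrawal** states that children are "excluded from the study if they fail to attend either their baseline assessment or withdraw prior to the commencement of the immediate" group. The next sentence reads "Primary analysis will use the intention to treat principle, using the last observation carried forward for participants who withdraw after commencement of intervention", referring to the immediate group.
- **Analyses** repeats the label: "Primary analysis will use the intention to treat principle, using the last observation recorded for participants who withdraw from the program". It does not restore the children removed under the withdrawal rule. It goes on to specify a linear mixed model for the COPM and describes that model as able to cope with incomplete data with no need to drop children.
- **Recruitment process and Randomisation** fix when allocation happens: "When two groups of four to six participants each are identified, they will proceed to randomisation". The two groups are then paired, and "they will be randomly assigned to either the immediate intervention group or the waitlist control group with a 1:1 block allocation". On enrolment, the text says "This process will continue until 60 participants complete baseline assessments and proceed to the" Sports Stars group.
- **Sample size** counts differently: "60 participants (30 in each group) will be recruited to allow for 20% attrition".

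**The concern.** Intention to treat means analysing every randomised child in the arm to which the child was allocated. A rule that removes children for leaving after allocation but before the first session does not fit that label.

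The children removed need not be a random subset. The trial is described as assessor blinded only, and by design a family learns whether it starts now or waits. From the assessment schedule, T3 is at 5 months and T4, straight after the eight-week waitlist program, is at about 8 months. The wait is therefore roughly 5 to 6 months, and a waitlisted family has reasons to leave that an immediate-start family does not. The COPM goals are chosen by caregivers, so a family's motivation could plausibly affect both staying and scoring.

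At stake is the primary COPM comparison. It could become a comparison of those who stayed, reported under a label that says otherwise. Children excluded from the study would not be followed, so the size and direction of any selection could not be examined afterwards.

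**Working it through.** **1. Order of events.** Two groups are identified, the envelope is drawn, and only then is one of them the immediate group. Its start therefore always follows allocation, so the window before that start includes time after randomisation. For the pre-start withdrawal limb, this holds whether baseline comes before or after randomisation. For the missed-baseline limb the order matters: if baseline comes first, that exclusion precedes randomisation and does no harm. The text does not state the order outright, and the flow chart is not available here.

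**2. The plan's own sample size.** Inputs from the Sample size section: the previous study "showed a standard deviation of 1.87/2.88 (intervention/control"), difference 2 points, alpha 0.05, power 80%.

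- Pooled SD = √((1.87² + 2.88²)/2) = 2.428.
- The exact two-sided two-sample t calculation gives 25 per group (power 81.4%), and the normal approximation gives 24. The stated 25 reproduces.
- 50 × 1.2 = 60, the stated total.

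The concern does not rest on these figures. They supply the SDs used below.

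**3. How many randomised children could fall outside the set.** The protocol gives no pre-start withdrawal rate, so p is an assumption. For 60 to proceed, 60/(1 − p), rounded up, must be randomised.

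| p | Randomised | Outside the set |
|---|---|---|
| 5% | 64 | 4 |
| 10% | 67 | 7 |
| 15% | 71 | 11 |
| 20% | 75 | 15 |

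**4. Possible bias.** If a fraction q of an arm is excluded and those children differ by D points in COPM change from those kept, that arm's mean shifts by q × D. For a common D, the between-arm shift is b = (q₁ − q₂) × D.

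With 30 analysed per arm and children treated as independent, SE = √((1.87² + 2.88²)/30) = 0.627.

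Two-sided type I error = 1 − Φ(1.96 − b/SE) + Φ(−1.96 − b/SE).

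Both q and D are assumptions; D is set at half of, and one, control SD.

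| Loss, one arm vs other | D | b | Share of 2 points | Type I error |
|---|---|---|---|---|
| 10% vs 0% | 1.44 | 0.14 | 7% | about 5.6% |
| 10% vs 0% | 2.88 | 0.29 | 14% | about 7.5% |
| 10% vs 5% | 2.88 | 0.14 | 7% | about 5.6% |
| Equal, similar children | any | 0 | 0% | 5% |

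A separate simulation used 10% to 20% loss in one arm only and D of 1 to 2 points. The shifts were 0.1 to 0.4 points, with type I error about 5.0% to 9.5%.

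**The case against.** The strongest reply is that the effect may be negligible. The inclusion criteria require families to commit to the sessions and assessments, and groups are formed only from children who can attend a set day and place; both should limit early loss. The protocol does not give the interval between allocation and start, or say when families learn their arm. The exclusion rule applies to both arms, and only a difference between them produces bias. All of this stands. It limits the size of the problem but does not reconcile the rule with the label.

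A reader might infer more than the text supports:

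- *That the analysed arms will certainly differ from those randomised, or that the result will be biased.* The first needs at least one early withdrawal; the second needs withdrawals that differ by arm and relate to outcome.
- *That continued enrolment is itself a source of bias.* It adds whole pairs, each freshly randomised, and does not replace children within an arm. Any bias comes from the exclusion.
- *That early losses will go unreported.* The protocol commits to a CONSORT flow diagram, and nothing says these losses will be left out of it.
- *That the Sample size section counts the 60 at randomisation.* It says recruited, which does not settle the point.

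It can also be said that a family leaving the study may decline T2 and T3, that a baseline value alone adds little to the treatment contrast, and that last observation carried forward would give such a child zero change. This is fair. The gain comes mainly from children who leave the program but agree to be assessed, and from having the full randomised set on record.

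**Conclusion.** The contradiction is real, and nothing else in the document cures it. The withdrawal rule permits post-randomisation exclusions from an analysis called intention to treat. That conclusion rests on the text alone.

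Bias is conditional. On the assumptions shown, a one-arm loss of 10% shifts the difference by 0.14 to 0.29 COPM points, and losses that are equal and similar shift it by zero. The document supplies neither the rate nor the prognostic difference, so these figures illustrate and do not predict. The missed-baseline exclusion is a problem only if baseline follows randomisation. The point should be fixed because the change is cheap and data from children who are not followed cannot be recovered later; it does not show that the trial's result would be invalid.

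**What to change.** - In Criteria for withdrawal, delete the exclusion for withdrawal before the immediate group starts.
- In Analyses, define the primary set as all randomised children in their allocated arm, whether or not they start the program or stay on the waitlist.
- Keep every child with a T1 COPM in the planned mixed model. Offer T2 and T3 to those who leave the program but agree to be assessed.
- Report by arm, with reasons, any randomised child without a baseline COPM, since there are no goals to score.
- State in Sample size and in Randomisation the same point at which the 60 are counted.
- Use the set that proceeded to the group only as a labelled sensitivity analysis.

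If the exclusion were kept, the least that would be needed is to call the set modified intention to treat, report pre-start exclusions by arm and add a sensitivity analysis. That corrects the label but leaves the possible selection in place.

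The cost is wording, a few extra visits, and slight dilution of the estimated effect by children who never start.
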